### Data collection and management

All data are entered in data collection instruments in REDCap. REDCap provides features to maintain data quality. All variables are enforced a validation standard on the field. Validation prevents users from entering data in an incorrect format, as saving the data is impossible if data fails to match the validation format. Range checks are applied on all number fields so REDCap will warn the user if an entered value is out of the expected range. Also, some data collection instruments have validated branching logic and/or calculations built in. Warnings are given by REDCap when leaving a data collection instrument if not all data fields are filled in to prevent missing data. After completion of the study, the data will be stored in REDCap until 31st of January 2029.

The calendar function in REDCap is used to create reminders for contacting participants 90 days postoperatively. This is to ensure that any complication or adverse events handled out of the hospital is captured and to ensure participants to answer QLQ. The eCRF is stored in a REDCap electronic data capture tools hosted at the Capital Region of Denmark. The database is password-protected and only accessible to assigned persons. All participants are given a unique study identification number to extract pseudo-anonymized data from REDCap to statistical software programmes. Furthermore, identifying information on participants in REDCap will be marked by a “participant identifier” and this information cannot be extracted from the database. Written consent forms are stored in a locked filing cabinet.

### Statistics

For the primary outcome, the proportion of participants with unplanned unblinding before discharge in the two treatment arms will be calculated using descriptive statictics. The number of participants guessing the correct method of operation at unblinding beyond the level of chance is calculated using Bang’s Blinding Index [25].

Analyses and data summaries will be conducted using the groups to which the patients were randomised, and patients will be included regardless of whether they received the allocated treatment, or they were unblinded during admission (“intention to treat”). Baseline characteristics of the included patients will be summarised by trial arm using descriptive statistics with continuous variables reported as the median and interquartile range (IQR) and categorical values in numbers and percentages of the total group. Full details will be described in the statistical analysis plan for the study.

We expect the amount of missing data to be low as most data is extracted from the EHR. We also expect dropouts to be low given the non-experimental design of the study with no extra planned physical visits out of the ordinary follow-up. In the case of dropouts, we expect these to be “missing not at random.” Therefore, multiple imputation will be used for handling missing data.

The protocol, template for the eCRF including the data collection instruments, de-identified data, and the statistical code are not made publicly available but will be delivered upon reasonable request by contacting the PI or the corresponding author. However, access to de-identified data will require an application to and approval from the Danish Data Protection Agency.

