## Methods/design

This study is designed as a randomised, controlled, patient, and care provider blinded single-centre feasibility study with 1:1 ratio allocation of participants to either ORC or iRARC. We will enrol a total of 50 participants. The clinical assumption is that the planned sample size is sufficient to explore the primary outcome and describe if blinding is feasible [15].

This trial is registered on the 6th of June 2019 at ClinicalTrials.gov ID: NCT03977831 (https://clinicaltrials.gov/ct2/show/NCT03977831?term=NCT03977831&draw=2&rank=1). The protocol version is the original from the 14th of December 2018: Protocol-60292_v1_141218. The protocol for this randomised trial is reported in compliance with the Standard Protocol Items Recommendations for Interventional Trials (SPIRIT) guidelines (see appendix for SPIRIT checklist) [16].

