#### Quality of life (QoL)

To assess QoL participants will complete the validated EORTC QLQ-C30 and EORTC QLQ-BLM30 at baseline and 90-days postoperatively. EORTC QLQ-C30 has well-established reliability and validity and is frequently used in clinical trials of RC. EORTC QLQ-C30 is however not bladder specific. Therefore, QLQ-BLM30 will be used as an addition. This questionnaire has been used in several publications before but is not validated. Since most studies use the EORTC QLQ-C30 and QLQ-BLM30 comparative integration of the results in the existing literature will be easy. Patient-reported outcomes are reported according to standards recommended by the 2010 Consolidated Standards of Reporting Trials (CONSORT) PRO extension [23].

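### The protocol gives an expectation of missing-not-at-random dropout as its reason for unqualified multiple imputation, which in standard form assumes missing at random; the likely effect is small and mainly on day-90 outcomes

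*Protocol article*

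**What the plan says.** The Statistics section makes three statements about missing data.

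- Amount: "We expect the amount of missing data to be low as most data is extracted from the EHR", and "We also expect dropouts to be low given the non-experimental design of the study". No percentage is given for either.
- Mechanism and method, the second offered as following from the first: "In the case of dropouts, we expect these to be “missing not at random.” Therefore, multiple imputation will be used for handling missing data".

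No MNAR form of imputation and no sensitivity analysis is named. For the analysis as a whole the section adds: "Full details will be described in the statistical analysis plan for the study". No other section discusses the missingness mechanism.

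Two other sections show which data could be lost. Under Quality of life: "To assess QoL participants will complete the validated EORTC QLQ-C30 and EORTC QLQ-BLM30 at baseline and 90-days postoperatively". Under Data collection and management, REDCap reminders prompt a contact with each participant at day 90, both to pick up events treated outside the hospital and to obtain the questionnaires.

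**The concern.** Standard multiple imputation fills a missing value from the distribution seen in comparable patients who were observed. It is valid when, given the variables in the imputation model, dropouts do not differ systematically from those who stayed. MNAR means that they do. Expecting MNAR is therefore a reason why standard multiple imputation is not enough by itself. The article gives it as the reason for using the method.

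This is a stated inference that is wrong as written. It is not a detail left for later, and an analysis plan that follows the sentence would inherit the mismatch. A report could then say that the expected MNAR dropout had been handled when its bias was still there.

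A patient lost before the day-90 contact loses the second questionnaire, which the health record cannot supply, and possibly also complications treated elsewhere. Comparing these outcomes between arms is a secondary objective, and the article plans separate publications for the 30- and 90-day complication rates and for quality of life.

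**Working it through.** The plan attaches no figure to this point, so there is none to reproduce. The check asks how much bias standard multiple imputation leaves under MNAR.

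**Inputs from the article.** 50 participants ("We will enrol a total of 50 participants") allocated 1:1, so 25 per arm. Dropout is expected to be low, with no rate given.

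**Assumed inputs.** Baseline-to-outcome correlation r = 0.5; no true difference between arms; dropout only among patients with below-median outcomes; dropout rates as listed below.

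**Step 1: general formula.** Let d be the dropout fraction in an arm, and let dropouts be delta SD worse than comparable completers.

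- Bias in the arm mean = d × delta.
- Bias in the arm difference = d1 × delta1 − d0 × delta0.

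With delta = 0.5, an arm mean is off by 0.05 × 0.5 = 0.025 SD at 5% dropout, 0.10 × 0.5 = 0.05 SD at 10%, and 0.20 × 0.5 = 0.10 SD at 20%. If both arms have the same d and the same delta, the bias in the difference cancels, although both arm means are still too favourable.

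**Step 2: the below-median scenario by hand.** The below-median half of a standard normal distribution has mean −0.80. The mean of completers is therefore too high by 0.80 × d/(1 − d).

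- 20% dropout: 0.80 × 0.20/0.80 = 0.20 SD.
- 5% dropout: 0.80 × 0.05/0.95 = 0.04 SD.
- Difference among completers: 0.20 − 0.04 = 0.16 SD.

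Conditioning on baseline removes about r² = 0.25 of this, which leaves 0.75 × 0.16 = 0.12 SD in favour of the arm with more dropout.

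**Step 3: simulation of the same scenario** (regression on arm and baseline, the limit of MAR imputation).

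| Dropout by arm (assumed) | Bias in difference, SD | Coverage of 95% interval |
|---|---|---|
| 5% v 2% | 0.016 | 95.1% |
| 10% v 5% | 0.036 | 94.5% |
| 15% v 5% | 0.077 | 94.0% |
| 20% v 5% | 0.116 | 93.4% |
| 10% v 10% | about 0 | not reported |

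The standard deviation of the estimated difference is about 0.26 SD, so the largest bias is 0.116/0.26 = 0.45 of a standard error.

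**Step 4: proper multiple imputation, one arm** (20 imputations, 3,000 replicates). When dropout does not depend on the outcome, bias in the arm mean is 0.004 SD with simulation error 0.004. When it does (log-odds of 1 to 2 per SD), bias is 0.04 to 0.07 SD at 5% dropout, 0.08 to 0.11 SD at 10%, and 0.13 to 0.21 SD at 20%. The method works under its own assumption and fails under the one the article states.

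**Step 5: a binary day-90 outcome.** Suppose 3 of 25 are missing in one arm and 1 of 25 in the other. The difference in proportions can then move over a range of 3/25 + 1/25 = 4/25 = 16 percentage points between the best and worst assignment of the missing values.

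**The case against.** The strongest reply has four parts.

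1. **Multiple imputation can be run under MNAR.** Delta-adjusted and pattern-mixture versions exist, the article names no version, and the analysis plan is not shown. This stands as far as it goes. A reader might infer that multiple imputation can never be used under MNAR, or that the trial's estimates will be biased; the article supports neither. What it shows is an unqualified method justified by a mechanism that its standard form does not accommodate. Leaving details to the analysis plan does not undo that reasoning.

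2. **The bias is likely to be small.** This stands. The article expects little missing data, most of it comes from the health record, and day-90 contacts are prompted. Even at an assumed 20% v 5%, the bias is under half a standard error and coverage is still 93.4%.

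3. **The exposed outcomes are secondary.** This stands too. It is a feasibility study of blinding, and its primary outcome closes at discharge. Length of stay, blood loss, recovery-unit complications and delirium are recorded in hospital.

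4. **The primary outcome is not shown to be imputed.** Because the sentence names no outcome, a reader might infer that missing guesses of the operation would be imputed, and that these would be missing mainly in very ill or reoperated patients. The article says neither. The sentence follows from a remark about dropouts. The primary outcome has its own methods (descriptive statistics and Bang's Blinding Index). Guesses are collected at unblinding, with an option for not knowing.

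These arguments limit the reach of the point. They do not repair the sentence.

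**Conclusion.** The point holds as a wrongly reasoned sentence in the Statistics section. Standard multiple imputation would leave the bias that the article itself expects, mainly in day-90 quality of life and in complications handled outside hospital.

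The size depends on dropout rates and an MNAR strength that the article does not give. In the assumed scenarios the arm difference is off by about 0.02 to 0.04 SD for 5% v 2% to 10% v 5% dropout, and by about 0.12 SD for 20% v 5%. It is close to zero when dropout and its mechanism are the same in both arms. No conclusion about the feasibility of blinding rests on this sentence. Severity is minor to moderate.

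**What to change.** Replace the sentence with two statements.

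1. Multiple imputation is the working analysis for missing data, and it assumes missing at random.
2. Because dropout is expected to be missing not at random, the day-90 outcomes also get an MNAR sensitivity analysis. For quality of life, use delta-adjusted imputation, with the shift varied separately by arm over a range set in advance. For 90-day complications, use best-case and worst-case bounds.

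The range of shifts should be chosen and justified by the trial team, since the article offers no basis for a particular value. If missing at random was what the authors meant, the wording of the mechanism should be corrected as well.

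The cost is one paragraph of text and a few extra analysis runs. No new data are needed.

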### Monitoring

As this is a single-centre feasibility study no coordination centre or various committees are planned. The PI, [name], [name], [name], and HK have been in constant contact and have had arranged meetings approximately every third month to discuss progress, data quality, and potential challenges in the conduction of the trial. No data monitoring committee is planned due to the exploratory nature of the study design. Furthermore, the risk profile of the trial design is assessed to be minimal. The PI will make safety and progress reports to the ethics committee at least annually and within 90 days of study termination or completion. In case of serious adverse events beyond what can be expected from RC, the ethics committee will be notified immediately, and no longer than 2 weeks after.

### Ethics and dissemination plans

The Danish Scientific Ethical Committee System (journal number: H-18056682) has approved the trial. The PI will be responsible for any amendments to the protocol. Any modifications will be reviewed and approved by the Danish Regional Ethics Committee. In this case, the protocol name will be changed so the suffix will indicate the version number and new date (e.g., v2_ddmmyy, v3_ddmmyy). A list of amendments will be created to keep track.

Both ORC and iRARC in a modified ERAS protocol are offered as standard treatments at the Department of Urology, Rigshospitalet, and is provided for by the Danish healthcare system. No participants are subjected to any kind of experimental treatment. Therefore, we do not expect any harm from the trial. All areas in the Danish healthcare system are covered by a publicly funded compensation scheme. All participants can file a claim for an injury sustained as a result of the treatment through the Patient Compensation Association as everyone else who receives treatment or purchases medicine in Denmark.

The trial results will be published in peer-reviewed international journals or otherwise made publicly available and will be presented at national and international conferences and symposiums irrespective of the outcomes. In a 30- and 90-day complication rates, QoL and PACU complications will be reported in separate publications. Study completion is expected by March 2021, and dissemination of the results will begin as soon as possible thereafter.

## Discussion

RC remains among the most complex urological procedures with a high risk of short- and long-term morbidity and mortality. Advancements in technology, urologic and anaesthesiologic care, and structured protocols for enhanced surgical recovery have aimed to reduce complications after RC. In the past decade, the evolution of surgical robots has fueled the interest for laparoscopic surgery and has encouraged the surgical community to anticipate that robot-assisted laparoscopic surgery is superior to open surgery, especially in terms of complications and recovery. However, with both patient safety and increasing expenses in health care in mind, it is important to be critical when introducing new medical equipment and surgical techniques. Surgical trials are difficult to successfully undertake and pose specific practical and methodological challenges [26]. The IDEAL collaboration has formed a framework for the assessment of surgery based on a five-stage description of the surgical development process [27]. These recommendations offer good practical guidance. Unlike areas of pharmaceutical interventions, the evaluation of surgical interventions with RCTs is not mandatory, and most likely, the absence of a regulatory framework has contributed to the proliferation of surgical innovation based on limited and weak scientific evidence.

To date, four RCTs have compared ORC to RARC [5–8]. Nix et al. reported the first trial of ORC versus RARC in 2010 [5]. It was a non-inferiority trial investigating the lymph node yield between the two procedures and demonstrated that RARC was non-inferior to ORC. The study also showed a significant difference in EBL, time to flatus, time to bowel movement, and use of inpatient morphine sulphate equivalents in favour of RARC although operative time favoured ORC. The study found no significant difference in the overall complication rate or LOS. Both Bochner et al. in 2015 and Khan et al. in 2016 investigated ORC versus RARC with complications as the primary outcomes [6, 8]. Bochner et al. reported the overall 90-day grade II–V Clavien-Dindo complications as primary outcome and found no significant difference between ORC and RARC [6]. Results from secondary outcomes included a significant difference in operative time and costs in favour of ORC and EBL in favour of RARC. No significant difference was found in high-grade complications, pathological outcomes, or QoL between the two arms. Oncological outcomes such as the risk of recurrence, patterns of recurrence, and survival did not differ between ORC and RARC [28]. Khan et al. compared laparoscopic RC, RARC, and ORC for complications (Clavien-Dindo) at 30 and 90 days after surgery and found no difference in complication rates between ORC and RARC. Operative time favoured ORC, but no significant difference was found in other secondary outcomes. The most recently published trial of ORC versus RARC is the RAZOR trial [7]. It was a non-inferiority trial with progression-free survival at 2 years as the primary outcome demonstrating RARC to be non-inferior to ORC. Of significant secondary outcomes, they found a difference in EBL, postoperative blood transfusion, and LOS in favour of RARC and a significant difference in operative time in favour of ORC. No significant difference was found in overall complication rate, major complication rate or QoL.

In the previous RCTs, the urinary diversion for RARC has been performed extracorporeally. A completely intracorporeal procedure could potentially hold advantages over ORC. This is currently being investigated in the ongoing iROC trial which is designed to show a difference in recovery in terms of DAOH [29]. However, this trial is not blinded. The lack of blinding may cause bias, especially if the level of subjectivity in the outcome variable is low. In trials comparing laparoscopic and mini-laparotomy cholecystectomy, non-blinded RCTs found a shorter recovery in terms of LOS and time back to work with the laparoscopic technique [30, 31]. However, in a blinded RCT of laparoscopic versus mini-laparotomy cholecystectomy no difference in outcomes was found [32].

None of the previously conducted studies has the perioperative care been described as standardised in an ERAS setup. ERAS focus on promoting recovery by reducing the surgical stress response and postoperative organ dysfunction. We believe a blinded trial with a strict ERAS protocol in RC is necessary to further understand the true differences between RARC and ORC.

The success of the blinding in our study is dependent on two aspects. Firstly, the amount of “intentional” unblinding during admission to the hospital would reveal the method of surgery. Secondly, “unintentional” unblinding can happen if variables that reveal the used procedure are not masked. From previous RCTs, a significantly lower EBL is known with RARC and a shorter operative time with ORC [5–9]. Also, the surgical wound on the abdomen will reveal the used procedure. These factors might affect how mobilisation is advised, painkillers are administered, etc. It may also affect the patients’ experience and expectations for post-surgical care. Therefore, blinding in RC patients may reduce the many biases introduced in the previous RCTs. But blinding of surgical procedures is challenging at both patient and physician level. However, in abdominal surgery, it has been shown that blinding is feasible by covering the whole abdomen with a bandage [11–14]. In RC, the dressing also needs to consider the urinary stoma which poses a technical challenge. We solved this by designing a dressing, together with experienced nurses, which was tested before study initiation. We have also made detailed instructions for changing the dressing including a template for how to place the dressing. To maintain blinding, a nurse from the neighbouring ward is summoned if the dressing needs to be changed and a pillow will be placed on the patient’s chest to block their view of the wound. Patient instruction and practice in changing of the stoma appliance can be carried out as needed as the stoma is free of the customised dressing.

In short, this protocol describes the first trial that evaluates the feasibility of a blinded study comparing ORC and RARC in an ERAS setup. Evidence from studies of high methodological quality is much needed in the field of RC. Lessons learned from this trial could prove valuable for the design and execution of future trials.

### Trial status

The original first version from 14th of December 2018: Protocol-60292_v1_141218. The study was initiated in June 2019, and 47 participants have been enrolled so far. We expect completion of participant accrual in December 2020.

## Data Availability

After study completion and publication of the study, the dataset analysed during the current study will be available from the corresponding author on reasonable request and upon approval from the Danish Data Protection Agency.

## Abbreviations

RC: Radical cystectomy
BC: Bladder cancer
ORC: Open radical cystectomy
RARC: Robot-assisted laparoscopic radical cystectomy
iRARC: Robot-assisted laparoscopic radical cystectomy with intracorporeal urinary diversion
RCT: Randomised clinical trial
LOS: Length of stay
DAOH: Days-alive-and-out-of-hospital
EORTC: European Organisation for Research and Treatment of Cancer
QLQ: Quality of life questionnaire
PACU: Post-anaesthesia care unit
EBL: Estimated blood loss
EHR: Electronic health record
PI: Principal investigator
DASAIM: Danish Society of Anaesthesiology and Intensive Care Medicine
3D-CAM: 3-Minute Diagnostic Interview for Delirium Using the Confusion Assessment Method
eCRF: Electronic case-report form
